***Background Considerations:***

*Anticoagulation Therapy and Thromboembolic risk*

This is an issue independent of other treatment strategies. There is clear guidance about its use depending on CHADS score:

Familiarise yourself with the CHADS scoring system for initiation of anticoagulation therapy in patients with atrial fibrillation. The above papers are attached.

The Steering Committee recommends warfarinisation with an INR of 2-3 for patients with a CHADS score > 1.

***Symptomatic AF***

When patients are complaining of palpitation then clinical assessment will be required in many. They are likely to be only a minority of the total number of patients with AF. In the first instance discuss the details of symptoms over the telephone, consider all the issues to do with rate/rhythm control (see below) and anticoagulation and then after those have been addressed and actioned offer a consultation if symptoms continue*.*

***Rhythm Management Options***

You will know that atrial fibrillation has been classified as:

- paroxysmal
- persistent
- permanent,

Given the above, on diagnosis of AF on monitoring, ask:

- Whether the patient is taking appropriate antithrombotic therapy?
- Is the patient symptomatic?
- Is AF causing worsening heart failure?
- Is the atrial arrhythmia paroxysmal, persistent or permanent and if paroxysmal, is it
- first episode
- recurrence

***Strategy*:**

*Step 1:* Initiate appropriate anticoagulation regime.

*Step 2:* Consider device programming.

a) Therapy for AF may affect device parameters. Consider detection and discrimination parameters and discuss with technician staff. In particular decided whether the rate is sufficiently fast to:

- Satisfy the VT/VF detection rate and lead to inappropriate shocks?
- Inhibit biventricular pacing?

Again answer to these questions may require discussion with technical staff and cardiology consultant. If in doubt consult them.

1. Therapy for AF may affect patient surveillance. If this is newly diagnosed and the patient is asymptomatic then increase frequency of downloads to twice weekly (and discuss with supervising cardiologist) for 4 weeks until the clinical situation is clearer. As a simple rule, if this is newly diagnosed atrial fibrillation and a remote treatment change is instituted, then increase the frequency of follow up to weekly for 4 weeks post management change.

*Step 3:* Consider treatment plan which may be:

- Rate control scenario
- Rhythm control scenario

A decision needs to be made as to what is the long-term rhythm control aim.

The decision could be determined by a number of clinical features and should be discussed with the supervising consultant who can make an informed decision about the overall direction of treatment strategy. This will not need face-to-face patient encounters although implementation of the chosen clinical strategy may do so. It will be influenced strongly by the atrial fibrillation classification. Thus, your task to is to “classify” the atrial fibrillation and then consider with the supervising physician a treatment plan.

Rhythm Control: Paroxysmal Self Terminating Atrial Fibrillation

In this instance rhythm control strategy will be adopted. If amiodarone is commenced consider the possible effect of this drug on defibrillation efficacy (see below). There is relatively less experience of the use of dronedarone in this scenario but if it is suggested by the responsible physician ensure that surveillance is maintained according to developing standards. Selection of any other antiarrhythmic drugs should follow careful clinical discussion.

Rarely an atrial fibrillation ablation strategy may be considered. Specifically raise this issue with the responsible physician. Again ask for a primary care assessment to assess electrolytes and renal function. Consider the burden of AF and how much it is limiting application of CRT.

Rhythm and Rate Control: Recurrent Persistent Atrial Fibrillation

In this instance a rate control strategy may be appropriate but if the duration and recurrence of atrial fibrillation is unclear then a decision may be taken to adopt a rhythm control strategy in the first instance.

*In the rhythm control scenario:* Consider with the supervising physician the use of appropriate drugs/cardioversion. Cardioversion may be considered using the device implanted to deliver the shock therapy. If amiodarone is commenced consider the possible effect of this drug on defibrillation efficacy (see below). There is relatively less experience of the use of dronedarone in this scenario, but if it is suggested by the responsible physician ensure that surveillance is maintained according to developing standards.

*In the rate control scenario:* Beta blockade will be the treatment of first choice. This could be commenced remotely in the absence of contraindications to beta blocker therapy – (check for these). Also assess whether there has been any other change in patient management recently and ask for a primary care assessment of electrolytes and renal function.

If already on adequate dose of beta blocker (and not on digoxin), consider digoxin, 500mcg bd for one day, then dose depending on age, weight and renal function. Ask for a primary care assessment to assess electrolytes and renal function.

Verapamil is a third line treatment.

In some circumstances AV node ablation may be the most reliable way of ensuring CRT therapy application and this should be specifically considered and discussed.

Permanent Atrial Fibrillation

A rate control strategy will be adopted. Assess any change in patient management recently and ask for a primary care assessment of electrolytes and renal function. Beta blockade will be the treatment of first choice. This can be commenced remotely though primary care in the absence of contraindications to beta blocker therapy – check for these. If already on adequate dose of beta blocker (and not on digoxin), consider digoxin, 500mcg bd for one day, then dose depending on age, weight and renal function. Verapamil is the third line treatment.

In some circumstances AV node ablation may be the most reliable way of ensuring CRT therapy application and this should be specifically considered and discussed.

Amiodarone is unlikely to be indicated.

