**Costs**

Costs of both implanted devices and conventional heart failure monitoring will be measured. These will include the costs associated with dealing with data obtained. Also measured will be all costs associated with providing heart failure related care in both arms of the study.

***Sample size calculations:*** Our sample size calculations use estimates from previous studies: i) Intervention group event rate: The Companion^38^ and Care HF^39^ trials with a patient population comparable to our study control group, reported 48% for any death or cardiovascular disease hospitalisation at 2 years, and 39% at 29 months for cardiovascular death or unplanned hospitalisation. We anticipate slightly lower rates in the proposed due to their receiving better routine care, and so assume a 40% event rate in the control arm by 2 years. ii) Overall risk reduction: The meta-analysis of Clark et al^10^ with telemonitoring or structured telephone support, reported a 20% risk reduction. Hence we will assume that the intervention group has a rate of 32%. This size of effect (40% reduced to32%) is clinically relevant. Assuming 5% (2-sided) significance and 90% power, 546 events are needed to detect this size of difference in a log-rank survival comparison of the two trial groups. This requires 1394 patients in total (697 per group). We will inflate this total by approximately 20% to allow for attrition, giving a target recruitment of 1650. This sample size is sufficient to estimate the effect size in the component outcomes - ACM, cardiovascular disease unplanned hospitalisation - and is feasible.

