**1 Introduction**

This handbook gives an overall guide to the interpretation of monitored data form implanted devices in patents with heart failure who are enrolled in the REM-HF study.

It supplements the Monitors’ Training Programme. This handbook will be used as an aide memoire during the two-week training course that will be delivered to all monitoring staff at study commencement and will therefore be supplemented by training material provided during the induction/training courses.

Whilst it endeavours to be comprehensive and give direction on interpretation of monitored data and appropriate clinical responses, it is not intended to entirely replace common sense clinical approaches.

The monitor should be prepared at all stages to consider discussion of the care issues with the supervising senior clinical staff.

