**2) Reporting Structure**

The Remote Monitor will access the monitoring websites and analyse downloads.

They will interpret the data or when necessary ask for assistance in data interpretation. The data comprises information about device functionality and about patient disease state.

Disease state is assessed by heart failure management status, atrial arrhythmia management, and ventricular arrhythmia management.

The different manufacturers’ devices have similar disease management potentials. The job of the monitor is to interpret the monitored data and communicate meaningful information to primary, secondary and tertiary care that will assist with patient management.

The case report forms for the study have the communication strategy for each patient identified.

Thus, at study enrollment the monitor will identify those colleagues with whom they must communicate for each patient. The services available to support patients differ between centres and therefore the clinicians who will action primary care/community-based therapy changes will differ between centres and within centres. However, the management change plan will be consistent across the study.

The monitor will interpret the download data, accessing support/help from the centres’ cardiac technicians/consultant cardiologists as wanted. The outcome of this process will sometimes be a management change. This may be:

- Drug change: actioned through nominated primary care contacts (GP/community heart failure nurse).
- Primary care test: (e.g. electrolyte estimation) actioned through nominated primary care contacts (GP/community heart failure nurse)
- Specialist test: actioned at the local centre
- Programming change or specialist intervention: actioned at the local centre

[figure not shown]

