The implanted devices are equipped with “Alert” facilities capable of recognising deterioration in either patient clinical status of change in device system functionality that may threaten system integrity/effectiveness. All Alerts will be programmed on but may be de-featured according to clinical judgement of the consultant cardiologist with clinical responsibility for the patient. This will not be a protocol violation but will be assessed in the study analysis.

In the event of an Alert being triggered then:

For non-automatic transmission the patient will contact the study nurse during office hours and perform a download.

The study nurse will inform the responsible senior clinician of all alert transmissions who will act on alerts and determine appropriate clinical action.

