### 4.4.1 Intervention cost

The intervention, remote monitoring, has to do with the provision of the monitors in each of the 9 sites. This excludes the cost of the devices fitted as these would be fitted anyhow. The direct cost of the remote monitoring will be personnel, seven of which were HF nurses (band 7) and two physiologists. These personnel worked partly on providing the intervention but also partly as researchers. Their research roles included recruitment, consent and data recording. Their remote monitoring role had to do with receiving and checking the weekly patient downloads and recommending changes as required. These elements have to be separated with only the costs of the intervention being relevant to the economic evaluation. The relevant cost is what the intervention might cost if applied in routine practice.

To separate these aspects, the relevant person at each centre was asked to identify the total time spent on REM and to divide this between that devoted to the intervention and that to do with the research, at the start and in early 2015. The time devoted to providing the intervention was aggregated by centre and multiplied by the staff cost, based on a HF nurse band 7 including overheads.

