## 7.5 Trial Timeline

## 7.6 Health economics: questionnaire and results (RMS)

### 7.6.1 Questionnaire sent to RMS

Please estimate the average number of hours per week the remote monitor role at your site is spending in each of the following three activity groups, both during the first year if you were employed at that time and again now. Please put a whole number in here not a range. It is just your estimate.

| **Site name:** | **Year 1** | **Year 3** |
| --- | --- | --- |
| **Download specific:**  *Reviewing the downloads*  *Initiating interventions as a result of the downloads* |  |  |
| **Research Specific Activity:**  *Screening patients*  *Randomisation and baseline visits*  *Research paperwork- GP information sheets, health questionnaires*  *ECRF data entry*  *Reporting SAEs and collecting source data*  *Follow up visits* |  |  |
| **Other:**  Any other activity or tasks such as other duties/mandatory training /meetings etc |  |  |

Thank you for completing this.

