### 7.6.2 Results of RMS survey

| Year 1 | Newcastle | Guys | Liverpool | Blackpool | Leicester | Leeds | Soothampton | Brompton | Manchester |  |  |
| --- | --- | --- | --- | --- | --- | --- | --- | --- | --- | --- | --- |
| Monitoring | 18 | - | 12 | 14 | 10 | 12 | 6 | 10 | - | 12 | 31 |
| Research | 18 | - | 25 | 20 | 28 | 35 | 25 | 12 | - | 23 |  |
| Other | 2 | - | 1 | 3 | 5 | 2 | 4 | 1 | - | 2 |  |
| total | 38 |  | 38 | 37 | 43 | 48 | 35 | 23 |  | 37 |  |
| Year 2 |  |  |  |  |  |  |  |  |  |  |  |
| Monitoring | 12 | 22 | 10 | 10 | 15 | 17 | 12 | 6 | 10 | 13 | 39 |
| Research | 18 | 15 | 27 | 22 | 21 | 16 | 20 | 5 | 15 | 18 |  |
| Other | 2 | 1 | 1 | 5 | 2 | 1 | 4 | 1 | 3 | 2 |  |
| total | 32 | 38 | 38 | 37 | 38 | 33 | 36 | 12 | 28 | 32 | 39 |

Of the 9 centres, 7 replied for year one, and all in year two. These replies put the mean number of hours in year one at 37, with 12 devoted to monitoring. Figures for year two were 32 and 13 hours per week, respectively.

For costing, the mean number of hours per week in each centre devoted to monitoring will be 12 in year one and 13 in year two.

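### The SAP costs remote monitoring as the monitors' own download hours, leaving non-contact consultant and technician time and the induction course uncosted

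*Combined protocol and SAP*

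**What the plan says.** **Costing.** Under SAP 4.4.1 each centre's monitor divides time on the study between intervention and research. The intervention part is summed by centre and "multiplied by the staff cost, based on a HF nurse band 7 including overheads". Seven of the nine monitors were heart failure nurses and two were physiologists. The survey in SAP 7.6.1 asks for "the average number of hours per week the remote monitor role at your site is spending" in three groups of activity. The group that is costed covers looking at downloads and starting whatever they prompt. SAP 7.6.2 then fixes the input: "the mean number of hours per week in each centre devoted to monitoring will be 12 in year one and 13 in year two". SAP 4.4.1 also sets the standard to be met, namely the cost of the intervention as an ordinary service would bear it. Of the costs to be measured, protocol section 10 (Costs) says: "These will include the costs associated with dealing with data obtained".

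**Delivery.** Protocol section 9 has the monitor co-ordinate care with consultant backing, and section 23 gives senior clinicians the job of reviewing troubleshooting and arrhythmia or heart failure data when the monitor asks. The handbook (Appendix II) adds detail:

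- Section 2: monitors interpret downloads with help from the centre's "cardiac technicians/consultant cardiologists as wanted".
- Section 4, Strategy: the long-term rhythm decision "should be discussed with the supervising consultant who can make an informed decision about the overall direction of treatment strategy", and device settings are talked over with technicians.
- Section 5: the monitor makes no therapeutic change for ventricular arrhythmia before talking to the responsible cardiologist.
- Section 6, Alerts: "The study nurse will inform the responsible senior clinician of all alert transmissions who will act on alerts".
- Section 1: there is a "two-week training course that will be delivered to all monitoring staff at study commencement".

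**The concern.** The intervention as described is a team activity, but the intervention as priced is one role. If consultants and technicians spend time on downloads without a patient contact resulting, that time is real NHS resource use on the remote pathway and enters no cost line. The same goes for the induction course. Cost per QALY is a listed secondary endpoint (SAP 3.2.2) and half of the trial's first objective (protocol section 5), and the result is to be read against NICE's £20,000 to £30,000. An intervention cost that leaves out part of the defined intervention makes remote monitoring look cheaper than the service an NHS commissioner would have to fund.

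**Working it through.** **1. Reproduce the plan's figures (SAP 7.6.2, monitoring rows).**

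- Year one, seven centres: 18 + 12 + 14 + 10 + 12 + 6 + 10 = 82; 82/7 = 11.71, rounded to 12. Share of all hours: 82/262 = 31%, as printed.
- Year two, nine centres: 12 + 22 + 10 + 10 + 15 + 17 + 12 + 6 + 10 = 114; 114/9 = 12.67, rounded to 13. Share: 114/292 = 39%, as printed.

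The costed hours are therefore the plain means of the monitors' own replies. Nothing for other staff has been added.

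**2. Look for the other inputs among the costed headings.**

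| Input to the remote pathway | Survey row costed (7.6) | Resource headings (4.4.2) | Total cost (4.4.4) |
| --- | --- | --- | --- |
| Monitor's download time | Yes | – | Yes, as intervention |
| Monitor's side of a staff discussion | Plausibly, as starting an intervention | – | Plausibly |
| Consultant's or technician's side, no patient contact | No: only the monitor role is surveyed | No: items are contacts, tests, admissions, drugs and device modifications | No |
| Visit or reprogramming that follows | – | Yes | Attendances are not named in this sum |
| Two-week induction course | No | No | No |

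SAP 4.4.2 costs each item as a count of contacts times a unit cost. The handbook (section 4, Strategy, Step 3) says the consultant's decision on atrial fibrillation can be made without seeing the patient. That decision therefore generates no contact to count.

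**3. Check for an offset from rounding.** Rounding up adds 12 − 11.71 = 0.29 h in year one and 13 − 12.67 = 0.33 h in year two. The average is 0.31 h, about 19 minutes of band 7 time per centre-week, or 25/24.38 − 1 = 2.5%. This works in the opposite direction to the omission but is small.

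**4. Put the omission on a scale (not an estimate).** The documents give no consultant or technician hours and no unit costs for them.

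- *Staff time.* The costed mean is (12 + 13)/2 = 12.5 h per centre-week. One further hour at the band 7 rate adds 1/12.5 = 8%. If the true figure were anywhere from 0.5 to 4 h (assumed), the addition would be 4% to 32%, multiplied by the ratio of the actual grade's rate to the band 7 rate.
- *Training.* Assume a 37.5 h week, so a course is 75 h of monitor time. Costed monitor time over two years is 25 × 52 = 1,300 h per centre. One trainee per centre adds 75/1,300 = 5.8% and two add 11.5%. This is a one-off cost before it is spread over its useful life, and it leaves out trainers' time.

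**The case against.** The other side has several good points.

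- *Follow-on work is already costed.* Visits, GP and nurse contacts and device modifications are in SAP 4.4.2. This stands, and it confines the gap to non-contact time plus training.
- *Some technical input is already inside the hours.* Two monitors were physiologists. This stands for their centres, but it does not reach consultant time.
- *Usual care has uncosted discussions too.* Protocol section 9 says usual pathways vary and that many centres already do remote technical checks. A reader might infer that the whole omission falls on the remote arm. The documents do not show that. Only time beyond usual device follow-up counts towards the difference, and the net amount is unknown.
- *Appendix I offers a price.* A reader might be tempted to value the missing time at the £100 per action in its scoping table. That figure prices actions and referrals, many of which become contacts already costed in 4.4.2, and no document gives a rate for staff discussions. It does not measure this omission.
- *The caseload sensitivity analysis.* SAP 4.4.5 varies monitoring cost by caseload. With fixed hours, halving caseload doubles cost per patient, so it can show whether the conclusion survives a dearer service. It cannot show that a staff group is missing or how much that group costs.
- *Training.* The survey's uncosted residual row mentions mandatory training, and a reader might infer that the course was recorded there and discarded. The row asks for average weekly hours and does not identify the induction course. What can be said is that the course has no cost line.

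**Conclusion.** The omission is real and the direction for the remote arm's intervention cost is clear: followed as written, SAP 4.4.1 and 7.6 understate it against the SAP's own routine-practice standard. Incremental cost is probably understated as well, because study downloads and alerts prompt discussions on top of unchanged usual device care; this rests on usual care not containing as much comparable time. The ICER is flattered only if incremental QALYs are positive. If they are not, incremental cost is still too low but the ratio does not read the same way.

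The size cannot be derived from the documents. The 8% per hour and the training percentages above are scales resting on stated assumptions, and no figure in pounds per QALY is supportable. The point affects the economic evaluation, not the primary clinical comparison. It should be corrected because correction is cheap and the definition of the intervention already includes these staff.

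**What to change.** In SAP 4.4.1, define intervention staff cost as three parts:

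1. monitor time, as now;
2. consultant and technician or physiologist time prompted by the remote arm's study downloads and alerts, limited to what is additional to usual device follow-up;
3. induction training, annuitised over a stated period.

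Add two rows to the SAP 7.6.1 survey, for consultant hours and for technician or physiologist hours per week on that work. Value them at grade-specific rates from PSSRU, a source the SAP already uses. At centres whose monitor is a physiologist, ask that hours already reported are not repeated.

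If centres cannot give usable estimates, add a named sensitivity analysis to 4.4.5 that varies this staff time over a range labelled as an assumption, separately from the caseload analysis.

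The cost is a change of SAP wording and one short repeat survey of nine centres. The downsides are that the replies depend on recall and that the ICER may come out slightly less favourable.
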